### 2.9.4. Qualitative Analysis

The interviews will be audio recorded and transcribed verbatim by an approved transcription service. Thematic analysis will be applied to code the data based on the pre-determined process evaluation topics (feasibility components) [67]. NVivo 12 will be used to analyse the transcripts (QSR International Pty Ltd., 2020). Transcripts will first be read and initial codes created based on the interview questions and research aims. OT will develop a preliminary coding framework and discuss this with PM, [name], and AM. Themes and sub-themes will be created both deductively and inductively, while making sure the theme labels remain representative of the data. To reduce bias, a sub-sample of the transcripts will be reviewed by a co-author and any discrepancies will be discussed and resolved. After all themes have been created, matrices will be developed to view responses and frequency of themes amongst the transcripts. To ensure rigour in the research, OT will engage in reflexive thinking throughout the research process. This will include discussing uncertainties with co-authors and constantly returning to the literature to elucidate particular themes or experiences. OT will endeavour to have spacing between interviews to allow for reflection and learning from each interview. To encourage participants to feel comfortable, interviews will be arranged for mutually convenient times and (if applicable) locations.

## 3. Discussion

The evidence base underpinning the effectiveness of nature-based play and learning provision suffers from poor methodological quality caused by a lack of well-designed evaluations [10]. We argue that evaluations can be better designed if a feasibility and pilot study is first carried out to address key uncertainties that may compromise a fully powered effectiveness evaluation. Feasibility studies are important for estimating recruitment and retention rates, data collection procedures and analysis, and acceptability of the programme [50]. The recent updated Medical Research Council (MRC) guidance on evaluating complex interventions recommends that key uncertainties should be investigated in a feasibility study and assessed against predefined progression criteria associated with the evaluation design and acceptability of the programme [37]. This in turn will ensure that finite resources are not wasted on under-powered large-scale evaluations. As outlined in this paper, this study will address key feasibility questions identified through programme theory work (Phase 1; Traynor et al., 2022) and collaborative engagement with key stakeholders (Phase 2; Evaluability Assessment). These include, recruitment and retention procedures, outcome measurement methods and analysis, and statistical matching procedures. Propensity score matching is a valuable method when randomisation is not possible within the study contexts [38]. Propensity score matching reduces the impact of bias on the outcomes under investigation by controlling for measured covariates. Nonetheless, this method does have its limitations such as the possibility of unmeasured covariates influencing the outcome of interest. Furthermore, our embedded process evaluation demonstrates a reliable theory-based approach for determining the acceptability of the study design methods and provision of the programme using NPT. Moreover, having pre-specified progression criteria based on a traffic light system for each research question demonstrates an explicit process to decide whether to proceed, proceed with modifications, or not to proceed for each trial procedure and programme [68].

Beyond addressing key feasibility aspects, our findings will have implications for the wider field of nature-based ELC research and any future fully powered effectiveness evaluation of outdoor nature-based ELC in Scotland. At present, evaluations often have a poor description of the dose and quality of their nature exposure element, making it difficult to determine the pathways by which nature-based ELC influence child health outcomes [15,18]. The present study has three clearly defined models of ELC (traditional, fully outdoors, and satellite) that differ in their provision of outdoor play and learning (e.g., time spent outdoors, number of children outdoors per session, and outdoor space used). Additionally, our observational methods and interviews will provide further detail regarding the affordances of each outdoor location with regards to environmental features and play behaviours. Therefore, alongside Gibson’s Theory of Affordances [69], these procedures will help a full-scale evaluation develop hypothesised pathways with outcomes to identify an effect, if one does exist. Furthermore, the role of the practitioner is also crucial within the provision of nature-based ELC [29]. Recent research has highlighted the need for more systems-based approaches with ELC practitioners to identify the factors important for implementing nature-based ELC (Zucca et al., under review). Our interviews with ELC practitioners and headteachers will contribute to our understanding of the specific pedagogical practices and contextual factors that influence how ELC educators support children’s outdoor nature-based play and learning experiences in nature. Finally, our findings will help policy makers and local authority decision makers optimise the resources they have by encouraging reflection on their current practice.

## 4. Conclusions

To support the implementation of outdoor nature-based ELC provision it is important for researchers to work collaboratively with practitioners and policy makers across the early years sector. This paper has demonstrated how we have developed a feasibility and pilot study to evaluate the provision of outdoor nature-based ELC, informed by collaborative engagement with key stakeholders and a research steering group. Our findings will demonstrate whether a quasi-experimental study design using propensity score matching is feasible and acceptable to take forward to a fully powered effectiveness evaluation. Furthermore, we will be able to identify to what extent outdoor play and learning provision has been normalised within early years practice and whether there are any key barriers to further normalising the provision of outdoor nature-based play and learning within Glasgow’s ELC settings. By involving our steering group within the decision-making process, these findings can help inform the implementation and subsequent evaluation of nature-based ELC settings across other parts of Scotland and the UK. 

## Figures and Tables

**Figure 1 ijerph-19-07461-f001:**
[figure not shown]
Study flow diagram. ELC—early learning and childcare; PA—physical activity; SDQ—strengths and difficulties questionnaire; PGMQS—preschool gross motor quality scale.

**Table 1 ijerph-19-07461-t001:** Outline of criteria, data collection tools procedures, study population, and analyses required for each research question.

Research Question	Criteria (How We Know We Have Achieved Objective) and Information Required	Data Collection Tools	Procedures	Study Population	Analyses
1. To what extent are the intended participants ***recruited*** to the study and ***retained***?	Data collected on eligible ELC settings, number that consent to take part, do not consent, and do not respond. Demographic characteristics, number that are retained or lost at follow-up	A map of ELC settings in GCC area will be used to identify eligible ELC settings. Email will be used for expression of interest. Setting demographics will be acquired via questionnaire. Parents will receive parent information sheet (PIS), consent form, and demographic characteristics questionnaire.	OT will approach eligible ELC settings via email with PIS, consent form, and letter of agreement, and a request for languages spoken at the nursery. These will be signed and returned if settings wish to take part. Flyers with QR codes will be distributed to parents. QR codes will give parents access to PIS, consent form, and surveys. Paper copies will also be available. The number of children who consent, do not consent, and do not respond will be recorded based on the number of returned consent forms. The number of retained participants and ELC settings will be recorded based on the number still participating at follow-up	Participating ELC settings in Glasgow and the children and staff attending them.	Calculate the number of consenting participants as a percentage of the total eligible ELC settings and children.
2. To what extent can ***propensity score matching*** based on multiple treatment groups be suitably applied within this context?	Data collected on number of children successfully matched across all participating ELC settings.	Children’s demographic information used for matching.	Observed covariates are recorded in both groups. A propensity score is calculated based on these characteristics. Propensity score of children in fully outdoor settings and satellite settings will be matched with propensity score of children in traditional ELC settings. The difference in average outcomes of the matched pairs are compared and a local average treatment effect is estimated. To reduce the risk of bias, matching will be combined with difference-in-differences method, facilitates correction of differences between groups that are fixed over time (reduces the risk of bias in the estimation).	Participating children in all participating ELC settings in Glasgow.	Average treatment effect will be calculated based on the propensity scoring matching of participants from each group.
3. What ***outcomes*** should be included in a future impact evaluation and how should they be measured?	Data collected on outcome measurements using, device worn measurements, questionnaires, and observations. Completeness of data collected and ease of use regarding measurement tools. Which outcome measurement tools identify a change in effect from baseline to follow-up (positive, negative, or null)?	Weight and height: portable standiometer and digital scales. Motor competence: Preschool Gross Motor Quality Scale (PGMQS)PA and sleep: Axivity device. Social and emotional outcomes: strength and Difficulties Questionnaire (SDQ). Play: Tool for Observing Play Outdoors (TOPO). Semi-structured interviews.	Baseline: weight and height, PGMQS, Axivity (7 days with a minimum of 3 full consecutive days), SDQ. TOPO will be implemented during exposure period. Follow-up: weight & height, PGMQS, SDQ, Axivity. Semi-structured interviews with managers and practitioners. Parents will be given a questionnaire at the end of the study asking how the SDQ and Axivity measurement tools were received.	Participating ELC settings in Glasgow, children, staff, and parents/carers.	Summary statistics will be presented for the outcome measures, means and standard deviations will be presented.
4. To what extent are current monitoing and evaluation **(*M&E) tools*** used within, and standardised across, ELC settings?	Monitoring and evaluation tools currently used at participating ELC settings will be examined to determine whether they can support measurement of outcomes and if analysis can be standardised across settings.	Learning journals (see-saw)	A sample of journals from each participating ELC setting (journals of participating children) will be collected and analysed for similar themes (e.g., are the same outcomes recorded, how often is information recorded in the journals, does the same practitioner record for the same child each time).	Participating ELC settings and participating (consent) children.	Thematic analysis to determine with a standardised framework can be developed for analysing journals to support outcome monitoring in a full-scale evaluation.
5. To what extent is the ***programme acceptable*** to ELC managers and practitioners?	Acceptability of programme implementation.	Semi-structured interviews with ELC managers and practitioners.	Purposive sample of managers and practitioners will be invited to interview, consent obtained, interviews recorded and transcribed.	Participating ELC settings, managers, and practitioners.	Qualitative interviews will be thematically analysed.
6. To what extent is the ***study design acceptable*** to ELC managers and practitioners?	Acceptability of trial methods including recruitment process and data collection methods.	Semi-structured interviews with ELC managers and practitioners.	Purposive sample of managers and practitioners will be invited to interview, consent obtained, interviews recorded and transcribed.	Participating ELC settings, managers, and practitioners.	Qualitative interviews will be thematically analysed.

**Table 2 ijerph-19-07461-t002:** Inclusion and exclusion criteria for the feasibility study of nature-based ELC.

Participant	Inclusion Criteria	Exclusion Criteria
ELC settings	Local childcare providers (nurseries, family learning centres, and preschools) in the GCC local authority area. The research team has a list of all ELC settings in the GCC area with their assigned data zone from the Scottish Index of Multiple Deprivation (SIMD, 2020). ELC settings that operate as traditional, satellite, or fully outdoors.	Childcare settings such as creches, child minders, playgroups, and au pairs/nannies. Not located in Glasgow, Scotland.
Children	Three years old at the time of recruitment or turning three during the study period (May to August 2022). Must spend at least three sessions per week (morning or afternoon sessions or all day) at the ELC setting included in the study. Children who have consent from their parents to participate. Specific to satellite settings: children who have attended their satellite outdoor space 3 times or less.	Not three years old at the time of recruitment or will not be three before the end of the study period (August 2022). Spend less than 3 sessions per week at the ELC under study. Have a serious injury or disability (e.g., wheelchair bound, broken leg, restricted arm movement) that would significantly limit their ability to engage in the study measurement methods. Children whose parent/carer does not provide informed consent to take part. Specific to satellite settings: children who have attended their satellite outdoor space more than 3 times.
ELC educators	Practitioners who supervise the children and support their play while outdoors. Managers/headteachers of participating ELC settings.	Practitioners who do not spend their working hours outside with the children when the children are outside (e.g., administrative staff).

**Table 3 ijerph-19-07461-t003:** Study criteria for progression to a powered effectiveness evaluation.

Feasibility and Pilot Study Criteria for Progression to a Powered Effectiveness Evaluation				
Research Question	Traffic light progression criteria	Recommendation if Green, Amber, or Red	Method of assessment	Rationale
1. To what extent are the intended participants ***recruited*** to the study and are they ***retained***?	Recruitment: *ELC Settings* GREEN: at least 30% of contacted ELC settings express a willingness to participate. AMBER: 10 to 29%. RED: less than 10% of contacted ELC settings respond. *Participants* GREEN: fully outdoor ELC settings, at least 50% of eligible children return a signed consent form. At satellite and traditional ELC settings, at least 25% of eligible children return a signed consent form. AMBER: at least 50% of fully outdoor ELC settings achieve their 50% recruitment target. At least 50% of satellite and traditional ELC settings achieve their 25% recruitment target RED: Amber target is not achieved	GREEN: Strong indication to use the same recruitment process in full effectiveness evaluation. AMBER: Indication that recruitment process might work, but should be discussed with research steering group. RED: Indication that recruitment process needs serious revision before full effectiveness evaluation.	Data collected on eligible ELC settings and participants, response rates, and non-response rates.	Based on recruitment and retention rates of past feasibility studies in UK early years settings (Barber et al., 2019; Kipping et al., 2019; Malden et al., 2019).
	Retention GREEN: 80% or more participant retention rate. AMBER: 50–79% participant retention rate. RED: less than 50% participant retention rate.	GREEN: Strong indication to use the same recruitment process in full effectiveness evaluation. AMBER: Indication that recruitment process might work, but should be discussed with research steering group. RED: Indication that recruitment process needs revision before full effectiveness evaluation.		
2. To what extent can propensity score matching based on multiple treatment groups be suitably applied within this context?	GREEN: 80% or more enrolled children suitably matched based on propensity scores. AMBER: 50–79% enrolled children matched. RED: less than 50% enrolled children matched.	GREEN: Strong indication that matching children based on their propensity score is a reliable comparison method to be used in a powered effectiveness evaluation. AMBER: Indication that the matching method might work in an effectiveness evaluation; however, it should be considered alongside other criteria such as the level of missing data. RED: The study design method needs careful consideration before being used again.	Determine the suitability of the covariates collected in the demographic survey are sufficient to calculate reliable propensity scores for matching.	We consider 80% to be achievable if the criteria regarding retention in RQ1 is successful.
3. What ***outcomes*** should be included in a future impact evaluation and how should they be measured?	GREEN: 70% or more measures are returned fully completed at baseline and follow-up. Outcome measures are able to identify a change from baseline to follow-up and a difference in effect between intervention and comparison groups (positive or negative). No major acceptability issues during educator interviews or via parent feedback. AMBER: Outcome measure completion rate of 60% or more. An indication that there may be a difference in effect but insufficient data to determine definitively. Three or four major acceptability issues raised by interviewees or through parent feedback; however, mitigating strategy identified. RED: Less than 60% of outcome measures completed. Major acceptability issues raised regarding measurement methods with no possible mitigation strategy.	GREEN: Strong indication to proceed with the outcome measurement methods. AMBER: Medium indication to proceed. Recommend discussing the measurement methods with research steering group. RED: Indication of doubt as to whether to proceed. Measurement methods should be discussed with steering group, taking into consideration findings from RQ6 and whether different measurement tools might be better suited to detect an effect in outcomes.	Baseline and follow-up outcome measures. Feedback from parents in activity diary. Process evaluation interviews with ELC educators.	We consider 70% completion rate sufficient to carry out analysis.
4. To what extent are current ***M&E tools*** used within, and standardised across, ELC settings?	GREEN: a standardised method of analysing M&E tools across ELC settings is identified and can be used for measuring specific outcomes in a powered effectiveness evaluation. AMBER: there is the potential to standardise the analysis of M&E tools across settings that would require minor changes within ELC practice. RED: there is considerable variation between ELC settings regarding the recording methods of outcomes and adapting practice would be counterproductive.	GREEN: Strong indication to proceed with M&E practices that are already in place to record and analyse some outcomes. AMBER: Medium indication to proceed. Recommend discussing the M&E methods with steering group and making a judgement on how to proceed. RED: Not likely to be an effective use of time or resources. Judgement as to how to proceed should be considered with steering group.	A sample of M&E practices from participating children at enrolled ELC settings.	Standardising the analysis of M&E practices already in place at ELC settings will reduce the burden on participating ELC settings in the next stage of evaluation.
5. To what extent is the ***programme acceptable*** to ELC managers and practitioners?	GREEN: analysis of interviews identify little (minor) to no barriers mentioned on supporting the provision of outdoor play and learning within the constructs of the Normalisation Process Theory. AMBER: three or four modifiable barriers identified within the constructs of NPT. RED: several major and non-modifiable barriers identified regarding the acceptability of outdoor play and learning among interviewed participants within the constructs of NPT.	GREEN: Strong indication that outdoor play and learning is becoming a normal practice for ELC practitioners and evaluation of the programme can proceed. AMBER: Indication that outdoor play and learning provision is not yet a normal practice across ELC settings. Findings should be considered with research steering group before proceeding with next stage of evaluation. RED: Doubt regarding whether outdoor play and learning provision is considered a normal practice among ELC practitioners and managers. Steering group should be consulted regarding whether knowledge of outdoor play and learning needs to be promoted among ELC educators before proceeding to an evaluation (e.g., education intervention).	Acceptability of the programme will be assessed through interviews with ELC headteachers/managers and practitioners using the four constructs of NPT (Coherence, Cognitive Participation, Collective Action, Reflexive Monitoring) as part of the process evaluation. See Appendix A for the interview guide.	A focus on major issues associated with the constructs of NPT is considered acceptable for qualitative data rather than quantitative targets.
6. To what extent is the ***study design acceptable*** to ELC managers and practitioners?	GREEN: analysis of interview data identifies little (minor) to no barriers on supporting the study design within the constructs of the NPT. AMBER: three or four modifiable barriers identified within the constructs of NPT. RED: several major and non-modifiable barriers identified regarding the acceptability of the study design among interviewed participants within the constructs of NPT.	GREEN: Strong indication that the study design methods are acceptable among early years educators and children and can be taken forward to a powered effectiveness evaluation. Recommendation as per green target of RQ2. AMBER: Indication that the interview responses should be discussed with the research steering group and a decision made on how the study design can be adapted to be less burdensome. Recommendation as per amber of RQ2. RED: Indication that study design is too labour intensive for participants and needs to be revised before progression to next stage of the evaluation. Recommendation as per red of RQ2.	Acceptability of the study design will be assessed through interviews with ELC headteachers/managers and practitioners using the four constructs of NPT (Coherence, Cognitive Participation, Collective Action, Reflexive Monitoring) as part of the process evaluation. See Appendix A for the interview guide.	A focus on major issues associated with the constructs of NPT is considered acceptable for qualitative data rather than quantitative targets.

**Table 4 ijerph-19-07461-t004:** Outcome measurement methods for the feasibility and pilot study.

Participant	Measurement Tool	Data Collection Timepoints at Participating ELC Settings		
		Baseline (Week 0)	Mid-Point	Follow-Up (Week 5)
Child	Parent/carer Demographic Questionnaire	🗴		
	Strength and Difficulties Questionnaire	🗴		🗴
	Height and weight	🗴		🗴
	Preschool Gross Motor Quality Scale	🗴		🗴
	Axivity (physical activity, sedentary time, sleep)	🗴		🗴
Headteachers/ practitioners	Play behaviours (TOPO)		🗴	🗴
	Semi-structured interviews			🗴
	ELC Monitoring and evaluation tools	🗴		

**Table 5 ijerph-19-07461-t005:** Balance tasks using the preschool gross motor quality scale (adapted from Sun et al., 2010).

Task Code	Balance Task	Criterion Code
B1	Single leg standing	A. Both hands remain on waist. B. Two legs do not lean against each other. C. Non-preferred leg keeps hip extension and knee flexion. D. Preferred leg stands on ground without moving for 5 s.
B2	Tandem standing	A. Both hands remain on waist. B. Postural sway forward and backward less than 30. C. Postural sway side to side less than 30. D. Feet contact ground more than 10 s. E. Feet contact ground more than 20 s.
B3	Walking line forward	A. Walks with each foot contacting the line fully. B. Does not open arms for balance. C. Steps on line precisely without trial. D. Continues heel–toe walking in line for 6 steps. E. Walks with each foot contacting the line fully.
B4	Walking line backward	A. Does not open arms for balance. B. Steps on line precisely without trial. C. Each step goes behind the previous one. D. Walks backward with standard position for 6 steps.

**Table 6 ijerph-19-07461-t006:** Categories of risky play (adapted from [24,25,26]).

Category	Description
*Play with great heights*	Danger of injury from falling from a height relative to the child’s own height such as forms of climbing, jumping, balancing from heights
*Play with high speed*	Uncontrolled speed relative to the child that can lead to a collision with someone (or something) such as on a bicycle, sliding, or running uncontrollably
*Play with dangerous tools*	Tools that can lead to injuries such as knives, hammers, or ropes
*Play near dangerous elements*	Such as a body of water or fire pit
*Rough-and-tumble play*	Where children can harm each other such as wrestling or fencing with sticks
*Play where children go exploring alone*	With the possibility of getting lost such as without supervision and where there are no boundaries or barriers
*Play with impact*	Children crashing into something repeatedly for fun
*Vicarious play*	Children getting excited from watching others engaging in risk

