### 2.2. Study Design

#### Feasibility and Pilot Study

The development of this feasibility study is based on guidance from the UK Medical Research Council for developing and evaluating complex interventions [37]. This study will pilot a quasi-experimental study design method:

A quasi-experimental non-equivalent control design using propensity score matching with multiple treatment groups. Children who attend two traditional ELC settings will be assigned to the control group and matched with children from two treatment groups: (1) 2 fully outdoors ELC settings and (2) 2 satellite ELC settings. The researchers will follow guidance on implementing propensity score methods with multiple treatment groups (e.g., 2 exposure groups and a control group) [38]. From baseline to follow-up, the study duration will be 5 weeks. Play and learning will continue as normal in both settings and the outcomes mentioned below will be measured to assess the possible impact of outdoor play and learning.

This study will employ a mixed-methods approach. Both quantitative and qualitative data will be collected to address the research questions. Alongside the piloting of these two study designs, we will carry out a process evaluation using semi-structured interviews. Qualitative methods are considered an important methodological approach to understanding the causal mechanisms of complex health interventions [39].

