### 2.6. Sample Size

As this is a feasibility/pilot study, no sample size to detect between group differences was calculated. The study may provide preliminary data for the calculation of a sample size for a future full-scale evaluation. We aim to recruit 2 fully outdoor ELC settings, 2 satellite ELC settings, and 2 traditional ELC settings.

A minimum of 10 children per ELC setting will be recruited. Two practitioners and one headteacher/manager will be recruited from each ELC setting.

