#### 2.8.1. Progression Criteria 

The CONSORT 2010 extension to randomised pilot and feasibility trial guidelines recommend setting out progression criteria when reporting feasibility and pilot studies [48]. In line with recommendations, our progression criteria will be assessed using a traffic light system with varying levels of acceptability, rather than strict thresholds [49,50,51]. For example, GREEN, strong indication that study design and programme is feasible and can be taken to the next stage of evaluation; AMBER, study design and programme could be feasible with some modifications; and RED, study design and programme should not progress forward without serious consideration and modification. The progression criteria for each RQ can be found in Table 3.

As demonstrated in Table 3, the progression criteria for **RQ1** have been informed by previous feasibility studies in this setting, where researchers have demonstrated a recruitment rate of 32%, 37%, and 10% of eligible ELC settings, respectively [31,32,33]. Our recruitment rate of at least 30% of contacted eligible ELC settings will demonstrate that our recruitment methods for ELC settings are feasible for a larger effectiveness evaluation. Moreover, to determine the feasibility of our participant recruitment methods, we aim to have at least 50% of eligible children at fully outdoor settings return a signed consent form and 25% of eligible children at all other settings return a signed consent. These estimates are different because we believe buy-in from parents at fully outdoor ELC settings will be greater than some of the traditional and satellite settings given the nature of the research project (exploring the impact of children playing outside). Additionally, parents choose to enroll their children at fully outdoor ELCs, whereas places at council-organised settings are assigned. Finally, if 80% or more participating children are retained at the study follow-up time period, the participant recruitment methods will be considered feasible to progress to an effectiveness evaluation. If less than 50%, the pilot study will be halted and will return to the design stage. If retention rates are between 50% and 79%, then the retention methods will be reviewed to determine whether they can improve before progressing to a powered effectiveness evaluation. 

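### The RQ2 traffic light pools matching over all three models, so good matching in one contrast can mask failure in the other

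*Protocol article*

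**What the plan says.** Table 3 of the protocol article scores RQ2 in three bands: "GREEN: 80% or more enrolled children suitably matched based on propensity scores"; "AMBER: 50–79% enrolled children matched"; and "RED: less than 50% enrolled children matched". None of them sets a minimum for a model or a contrast. The RQ2 measures in section 2.8 are the number of children given a score and the number of matches, again without a split. A GREEN result is read as strong support for using matching in the powered evaluation.

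The matching itself has two parts. Section 2.2 has traditional children "matched with children from two treatment groups: (1) 2 fully outdoors ELC settings and (2) 2 satellite ELC settings", and Table 1 (RQ2, procedures) says: "Propensity score of children in fully outdoor settings and satellite settings will be matched with propensity score of children in traditional ELC settings". The planned size is in section 2.6: "We aim to recruit 2 fully outdoor ELC settings, 2 satellite ELC settings, and 2 traditional ELC settings", and "A minimum of 10 children per ELC setting will be recruited".

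Two further statements bear on the count. Section 2.8.1 sends only retained children into matching, whereas Table 3 counts enrolled children. Section 2.9.3 names the average treatment effect (ATE) of attending nature-based provision as the quantity to estimate.

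**The concern.** RQ2 asks whether matching with multiple treatment groups can be applied in this context. That a satellite child has a comparable traditional child says nothing about whether a fully outdoor child has one. In a pooled percentage, matched satellite and traditional children can make up for fully outdoor children who have no match, or the reverse.

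The plan already separates models elsewhere in the same table: the RQ1 consent targets are 50% for fully outdoor settings and 25% for the others. RQ2 has no such split, although its colour decides whether matching goes forward as the comparison method. The risk is that matching is endorsed for a contrast in which the pilot showed it did not work.

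**Working it through.** **Inputs.** Two settings per model with at least 10 children each (section 2.6) give 20 per model and 60 in total. The bands are 80% and 50% (Table 3). The plan derives no sample size or power for RQ2, so there is no figure to reproduce beyond 6 × 10 = 60.

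**Rule as worded.** Share = (matched fully outdoor + matched satellite + matched traditional) / enrolled.

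**Base case.** All 60 are retained, all 20 satellite and all 20 traditional children are matched, and a traditional child may serve in both contrasts.
- GREEN needs 0.80 × 60 = 48 matched. The other two models supply 40, so 48 − 40 = 8 fully outdoor matches are enough.
- Fully outdoor alone: 8/20 = 40%, RED on the same bands, with 12/20 = 60% unmatched.
- No fully outdoor child matched: 40/60 = 66.7%, AMBER. AMBER needs 0.50 × 60 = 30, so it holds as long as 30 of the 40 other children are matched.

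**One assumption changed at a time.**

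| Variant | Fully outdoor matches needed for GREEN | Light with none matched |
|---|---|---|
| Base case | 8 of 20 | 40/60 = 66.7%, AMBER |
| Only exposed children counted | 32 − 20 = 12 of 20 (40% unmatched) | 20/40 = 50%, AMBER |
| 90% retention, enrolled denominator | 48 − 36 = 12 of 18 retained | 36/60 = 60%, AMBER |
| 80% retention, enrolled denominator | 48 − 32 = 16 of 16 retained (no masking) | 32/60 = 53.3%, AMBER |
| 80% retention, retained denominator | 0.80 × 48 = 38.4, so 39 − 32 = 7 of 16 (44%) | 32/48 = 66.7%, AMBER |
| Each traditional child used once, 1:1 | unreachable: at most 40/60 = 66.7% | 40/60 = 66.7%, AMBER |

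Combined changes can remove the AMBER result. Counting exposed children only, at 80% retention with the enrolled denominator, no fully outdoor match gives 16/40 = 40%, RED.

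**Unequal groups** (fully outdoor/satellite/traditional, otherwise as the base case). Ten per setting is a minimum, so sizes may differ in either direction.
- 20/30/30: GREEN needs 64/80, so 64 − 60 = 4 of 20 fully outdoor matches (20%).
- 30/20/20: GREEN needs 56/70, so 56 − 40 = 16 of 30 (53%), which is AMBER for that group.

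**Bands applied per contrast, base case.** Fully outdoor against traditional is 8/20 = 40%, RED. Satellite against traditional is 20/20 = 100%, GREEN.

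**The case against.** The strongest reply is that the GREEN example needs everything to go well elsewhere. At 80% retention, which is the plan's own GREEN line for RQ1, the enrolled denominator leaves no room for masking. With single-use controls GREEN cannot be reached at all. Both points stand, so the 60% figure belongs to a stated scenario and does not describe the rule in general.

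A second reply is that AMBER is not a pass. It calls for the result to be weighed with other criteria, and section 2.8.1 describes the lights as levels of acceptability instead of strict thresholds. This softens the zero-match case. But the example Table 3 gives of another criterion is missing data, and nothing in the table directs attention to matching by model.

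A third reply is that section 2.9.3 refers to one logistic model and one ATE for nature-based provision, which could mean a pooled exposure. Section 2.2, Table 1 and the RQ2 question all describe multiple treatment groups, and a pooled exposure would still hide an unmatched model.

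Three stronger readings are tempting, and the article does not support them.
- A reader might infer that the plan itself expects fully outdoor families to be hardest to match. Section 2.8.1 does say that "parents choose to enroll their children at fully outdoor ELCs, whereas places at council-organised settings are assigned", but only to explain a higher consent target. Weak overlap is a reasonable concern drawn from that self-selection; the plan does not state it.
- A reader might infer that actual recruitment will worsen the masking. The plan's higher consent target for fully outdoor settings could just as well make that group larger, and masking is then weaker, as the 30/20/20 case shows.
- A reader might object that the article does not say whether matches are counted as pairs or as three-way sets. That is counting detail which a fuller plan may settle, and the point does not rest on it.

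**Conclusion.** The point holds in a limited form. As worded, Table 3 allows matching to be rated favourably for RQ2 when it has failed in one of the two contrasts.

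The clearest case is GREEN with 8 of 20 fully outdoor children matched. It rests on four assumptions: equal groups of 20, full or nearly full retention, complete matching of the other two models, and reuse of traditional children across contrasts. It weakens or disappears when these change. Even then 8 pairs remain, so it would be wrong to describe that contrast as empty.

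The sturdier result is that the light is still AMBER with no fully outdoor child matched, in the base case and in each variant of the counting rule or retention taken singly. It requires the other models to match well. The same arithmetic applies with satellite and fully outdoor exchanged, so the flaw does not depend on which group proves harder to match.

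**What to change.** Reword the RQ2 row of Table 3 as follows.
- Apply the existing 80% and 50% bands separately to fully outdoor against traditional and to satellite against traditional, using the share of exposed children with a traditional match within the caliper.
- Let the lower share set the RQ2 colour, and give the recommendation per contrast, so that matching can go forward for one model if it fails for the other.
- Because the plan names an ATE, also report for each contrast the share of traditional children matched. Traditional children without a counterpart matter for that effect, and the exposed share alone would not show them.
- State whether the denominator is enrolled or retained children, and whether a traditional child may be used in both contrasts.

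This changes one table row and needs no new data. The light may be less favourable. Each share also rests on a smaller base: with 20 children one match moves it by 1/20 = 5 percentage points, against 1/60 = 1.7 points in the pooled figure.
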